### Subject Exclusion criteria

• Subarachnoid hemorrhage of other than aneurysmal origin

• No hemorrhage visible on initial CCT-scan (Fisher Grade I)

• Pregnancy

• Concurrent participation in another interventional trial (participation in an observational trial is not an exclusion criteria)

• Life expectancy less than 1 year for other reasons than the current SAH

• Other concomitant severe disease that would confound with treatment

• Other clear contraindication for treatment with a lumbar drain (e.g. absent or compressed basal cisterns on the admission CCT)

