### Interventions

In order not to provoke premature rupture of the aneurysm due to accidental drainage, randomization to the study and eventual placement of a lumbar drain takes place after securing the aneurysm by the preferred method of choice (Figure 1). Every patient in the lumbar drainage group (LD-group) receives a lumbar drain during anesthesia required for the aneurysm treatment. Insertion of a lumbar drain into the subarachnoid space is conducted in standard fully sterile technique. This is to be performed before anticoagulation or anti-platelet therapy is initiated, which sometimes is warranted after endovascular coiling. A post-procedural CCT scan of the brain is performed within 24 hours after aneurysm treatment. In case of neurological worsening after the procedure it is strongly recommended to perform the follow-up CCT-scan as soon as possible.

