If the post-procedural CCT or any other follow-up CCT scan shows compressed basal cisterns or any signs of threatening herniation, lumbar CSF diversion in the LD-group must not be performed. It may still be feasible to carefully drain CSF via the lumbar route [14], but this is at the discretion of the local investigator and not recommended. In patients requiring sedation and mechanical ventilation, either due to neurological impairment or for other medical reasons, intracranial pressure monitoring is mandatory. This may be performed according to local policy either with parenchymal or ventricular devices. If the intracranial pressure exceeds 20 mmHg, further CSF drainage via lumbar route shall be interrupted until the ICP is below 20 mmHg again. Careful CSF-drainage via the lumbar route may still be feasible in case of high intracranial pressure [14], but again this is at the discretion of the local investigator. A method of detecting the safety of lumbar CSF diversion may be determining the gradient of lumbar versus intracranial CSF pressure [15]. Albeit promising, the Earlydrain investigators explicitly rate this approach preliminary and experimental. In case of doubt, lumbar CSF diversion must not be performed.

Further neuromonitoring with transcranial duplex sonography (TCD), electroencephalography (EEG), brain tissue oxygenation recordings, jugular bulb oxymetry, regional cerebral blood flow measurement, microdialysis or other methods is at the discretion of the center and according to its local guidelines. As far as possible, this data should be saved electronically for post-hoc analysis.

A CCT scan as well as conventional digital subtraction angiography (DSA), CT angiography or MR angiography for assessment of vasospasm in the larger vessels is routinely performed on day 7 to 10 after the initial hemorrhage, according to local guidelines. In case of the occurrence of a DND when vasospasm is assumed to be the cause, angiography may be performed at any time. If it is performed earlier than day 7 to 10 and the patient shows no clinical deterioration thereafter, the angiography on day 7 to 10 is omitted. Treatment of radiographically confirmed vasospasm is according to local guidelines and not specified in the Earlydrain study protocol. It may include augmentation of cerebral blood flow via hypertensive hypervolemia as well as endovascular balloon dilation or intraarterial infusion of vasodilators.

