### Randomization

Any patient meeting the inclusion criteria and not violating the exclusion criteria may participate in the EARLYDRAIN study and be randomized to either receive a lumbar drain or not, thus defining the two distinct groups LD and NoLD.

Randomization is performed via a dedicated internet site accessible for all local investigators of the participating trial centers http://www.randomizer.at. No stratification or minimisation is to be used. The security measures of the online randomization system "randomizer.at" include that 1. All transactions are logged, 2. The audit trail of the trial can be accessed and analysed any time by the trial monitoring committee. 3. Network traffic between the web-browser and the randomizer is encrypted using SSL (*Secure Sockets Layer*) with strong encryption.

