### Safety of lumbar drains after aneurysmal SAH

In the above-mentioned two retrospective studies, mortality was lower in the lumbar drainage group. Neither of the retrospective studies mentions procedural related complications for the lumbar drains [12,13]. In patients with increased intracranial pressure, careful lumbar drainage of CSF may be a possible treatment even in case of compressed basal cisterns [14]. A feasible strategy to enhance safety is determination of the lumbar-cranial pressure gradient and cessation of lumbar CSF diversion in patients with increasing pressure difference [15].

However, in patients presenting increased intracranial pressure or compressed basal cisterns on CCT-scan the risk associated with lumbar drainage is unclear according to the current state of medical knowledge. In unclear cases the investigator must refrain from the insertion of a lumbar drain.

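### Eligibility removes only clear contraindications to a lumbar drain, yet the protocol also forbids insertion in unclear cases, so some patients can be randomised to a drain they may not receive

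*Protocol article*

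**What the plan says.** Four places in the protocol article bear on who may be randomised and who may receive the drain.

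- **Subject Exclusion criteria:** "Other clear contraindication for treatment with a lumbar drain (e.g. absent or compressed basal cisterns on the admission CCT". The scan finding is given as an example.
- **Randomization:** "Any patient meeting the inclusion criteria and not violating the exclusion criteria may participate in the EARLYDRAIN study".
- **Interventions:** "randomization to the study and eventual placement of a lumbar drain takes place after securing the aneurysm by the preferred method of choice". For the LD arm, "Every patient in the lumbar drainage group (LD-group) receives a lumbar drain during anesthesia required for the aneurysm treatment". No exception is stated there.
- **Safety of lumbar drains after aneurysmal SAH:** "in patients presenting increased intracranial pressure or compressed basal cisterns on CCT-scan the risk associated with lumbar drainage is unclear", followed by the rule "In unclear cases the investigator must refrain from the insertion of a lumbar drain". This rule speaks of insertion and says nothing about enrolment.

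Statistical Analysis plans both an intention-to-treat and a per-protocol analysis. The per-protocol set leaves out patients whose lumbar drainage departed from 5 ml/h, and controls who needed a lumbar drain.

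**The concern.** The entry screen and the insertion rule use different thresholds. Entry is blocked when the contraindication is clear; insertion is blocked already when the case is unclear. Patients between the two are eligible, but the allocated treatment is closed to half of them.

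The question whether a drain may go in then arises only after the arm is known, and only in the LD arm. Nobody asks it of a control, so comparable controls are never identified. Two things follow:

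- The primary comparison includes LD patients who did not get the treatment, which pulls the estimated effect towards zero.
- The per-protocol comparison could lose those LD patients while keeping their counterparts in the control arm. If unclear cases have a worse prognosis, that would favour the drain.

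**Working it through.** **Step 1. The wording side by side**

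| Patient state before randomisation | Exclusion criteria | Safety section | Interventions, if allocated to LD |
|---|---|---|---|
| Compressed cisterns on CCT | example of a *clear* contraindication: excluded | risk *unclear*: do not insert | drain for every LD patient |
| Raised intracranial pressure, not otherwise a clear contraindication | not listed: eligible | risk *unclear*: do not insert | drain for every LD patient |
| Any other doubtful case | not *clear*: eligible | do not insert | drain for every LD patient |

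The first row is a clash of labels: one finding is clear in one section and unclear in another. The second and third rows are the substantive conflict. The patient passes eligibility, the Interventions section requires the drain, and the Safety section forbids it. No section says that an unclear case must not be randomised.

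**Step 2. The plan's own power figure**

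Inputs from the sample size section: 300 patients in total, 50% versus 33% on the dichotomised modified Rankin Scale, alpha 5%, stated power 85.2%. Assumed: 1:1 allocation (150 per arm) and a two-sided test, neither of which is stated.

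Power = Φ{[d − 1.96·√(2p̄(1 − p̄)/n)] / √([p1(1 − p1) + p2(1 − p2)]/n)}, where d = p1 − p2 and p̄ is the mean of p1 and p2.

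With p1 = 0.50, p2 = 0.33, n = 150:

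- d = 0.17 and p̄ = 0.415
- null standard error = √(2 × 0.415 × 0.585/150) = 0.0569
- alternative standard error = √((0.25 + 0.2211)/150) = 0.0560
- power = Φ[(0.17 − 1.96 × 0.0569)/0.0560] = 0.852

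This matches the stated figure. A one-sided test would give 0.914, so the two-sided reading is the one that fits.

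**Step 3. Illustration of the dilution**

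Let a share f of the LD arm go undrained and have the control risk of 50%. The LD risk becomes 0.33 + 0.17f and the difference becomes 0.17(1 − f).

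| f (assumed) | LD patients, 150f | LD risk | Difference | Power |
|---|---|---|---|---|
| 0 | 0 | 33.0% | 17.0 points | 85.2% |
| 2% | 3 | 33.3% | 16.7 points | 83.7% |
| 5% | 7.5 | 33.9% | 16.2 points | 81.2% |

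The same formula solved for n at 85.2% power gives 151, 157 and 168 per arm. The sample size section names imbalance and the severity analysis as its reasons for going to 300; it mentions no allowance for undrained LD patients.

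**The case against.** The strongest reply is that this gap is small and that several wider readings are wrong. Those wider readings do fail:

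- **That only the admission scan counts.** The scan stands as an example. Cisterns compressed on a later scan before randomisation can be excluded under the same criterion.
- **That later scans forbid the drain.** The rule in Interventions that begins "If the post-procedural CCT or any other follow-up CCT scan shows compressed basal cisterns or any signs of threatening herniation" bars drainage of CSF, not insertion, and then partly leaves drainage to the local investigator. The drain is placed under the anaesthesia for aneurysm treatment and drainage starts after the post-procedural scan. A finding that arises after randomisation could not have been screened for at entry.
- **That earlier antiplatelet treatment bars the drain.** The text reads "This is to be performed before anticoagulation or anti-platelet therapy is initiated, which sometimes is warranted after endovascular coiling". It sets an order of events and does not say that a patient already treated may not have a drain.
- **That such patients can never be drained.** For pressure above 20 mmHg the protocol interrupts drainage until it is below that level again, and the abstract allows drainage to begin up to 72 hours after the aneurysm is secured. The obstacle may be temporary.
- **That a large loss of power is shown.** Shares of 10% or 20% have no basis in the documents and would also count patients barred only by later events, whom no entry criterion would remove.

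It is also fair that the planned intention-to-treat analysis keeps everyone, so no patient need be dropped from the primary comparison, and that clear contraindications are checked in both arms before allocation. The full protocol may already build a confirmation into the randomiser; the article does not say.

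What remains is the clash between the exclusion criteria, the Safety section and the Interventions section over cases that are already unclear before randomisation. The conflicting rules all stand in the article, so this is not a matter of detail left to a longer document.

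**Conclusion.** The concern holds in this limited form. As written, the protocol can randomise a patient whose drain it then forbids, and the forbidding judgement falls after open-label allocation in the LD arm alone.

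The intention-to-treat test keeps its validity; what it loses is power and a clean link between allocation and treatment. The per-protocol set, read literally, could lose such LD patients with no matching removal of controls; whether an undrained patient counts as departing from 5 ml/h is itself a matter of reading.

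The size cannot be established from the documents. The drop to about 84% or 81% power depends on an assumed 2% to 5% undrained share, a 50% risk in those patients, 150 per arm and a two-sided 5% test. The case for a change rests on the contradiction and the one-sided judgement rather than on those figures. It is a correction worth making, not a flaw that undermines the trial.

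**What to change.** 1. The sponsor should reconcile Subject Exclusion criteria, Interventions and Safety of lumbar drains after aneurysmal SAH, so that the same patient state has the same label and consequence in each. Which clinical rule is kept is for the sponsor and its clinicians; this review takes no position.
2. Whatever bars on insertion survive should be eligibility conditions, checked for every patient before allocation on information already available at that time.
3. Before the arm is shown, the investigator should confirm in the online randomiser that a drain could be inserted if allocated.
4. Rules on CSF drainage that are triggered after randomisation should remain treatment rules, and the patients they affect should remain in the intention-to-treat set.

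The cost is a reworded criterion and one confirmation field. No new scan or procedure is needed. A few patients now randomised would be screened out, so recruitment would be slightly slower.

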### Interventions

In order not to provoke premature rupture of the aneurysm due to accidental drainage, randomization to the study and eventual placement of a lumbar drain takes place after securing the aneurysm by the preferred method of choice (Figure 1). Every patient in the lumbar drainage group (LD-group) receives a lumbar drain during anesthesia required for the aneurysm treatment. Insertion of a lumbar drain into the subarachnoid space is conducted in standard fully sterile technique. This is to be performed before anticoagulation or anti-platelet therapy is initiated, which sometimes is warranted after endovascular coiling. A post-procedural CCT scan of the brain is performed within 24 hours after aneurysm treatment. In case of neurological worsening after the procedure it is strongly recommended to perform the follow-up CCT-scan as soon as possible.

**Figure 1 F1:**
[figure not shown]
**EARLYDRAIN study algorithm**. The EARLYDRAIN study algorithm showing the course of events after the initial aneurysmal subarachnoid hemorrhage (SAH) and the subsequent surgical or interventional aneurysm treatment. The study includes two groups, a treatment group receiving lumbar CSF-drainage (LD) and a control group receiving no lumbar drainage according to protocol (NoLD). The timing of the patient's consent to study participation, randomization, cranial imaging and assessment of clinical outcome is indicated by the shaded boxes. Imaging on day 7 to 10 is scheduled according to local guidelines. If a local center performs no routine cerebrovascular imaging for vasospasm screening in patients without clinical suspicion, it may be omitted.

In patients in the LD-group, CSF drainage via the lumbar drain is started slowly and steadily at a rate of approximately 5 ml per hour after the post-interventional CCT. This leads to a planned daily CSF-drainage of 120 ml per day through the lumbar route. Patients in both groups may receive additional CSF drainage via a ventricular device. The amount of CSF drained via the ventricular route is determined according to clinical requirement and not specified by the study protocol.

In order to enhance accuracy of the amount of CSF drained, regular drainage control every other hour and stopping in case of excess drainage is strongly recommended by the principal investigators. In case of neurological decline suspiciously related to the lumbar drainage, the drain must be closed immediately. Drainage may be gradually restarted after 12 to 24 hours, after performing a CCT scan.

If the post-procedural CCT or any other follow-up CCT scan shows compressed basal cisterns or any signs of threatening herniation, lumbar CSF diversion in the LD-group must not be performed. It may still be feasible to carefully drain CSF via the lumbar route [14], but this is at the discretion of the local investigator and not recommended. In patients requiring sedation and mechanical ventilation, either due to neurological impairment or for other medical reasons, intracranial pressure monitoring is mandatory. This may be performed according to local policy either with parenchymal or ventricular devices. If the intracranial pressure exceeds 20 mmHg, further CSF drainage via lumbar route shall be interrupted until the ICP is below 20 mmHg again. Careful CSF-drainage via the lumbar route may still be feasible in case of high intracranial pressure [14], but again this is at the discretion of the local investigator. A method of detecting the safety of lumbar CSF diversion may be determining the gradient of lumbar versus intracranial CSF pressure [15]. Albeit promising, the Earlydrain investigators explicitly rate this approach preliminary and experimental. In case of doubt, lumbar CSF diversion must not be performed.

Further neuromonitoring with transcranial duplex sonography (TCD), electroencephalography (EEG), brain tissue oxygenation recordings, jugular bulb oxymetry, regional cerebral blood flow measurement, microdialysis or other methods is at the discretion of the center and according to its local guidelines. As far as possible, this data should be saved electronically for post-hoc analysis.

A CCT scan as well as conventional digital subtraction angiography (DSA), CT angiography or MR angiography for assessment of vasospasm in the larger vessels is routinely performed on day 7 to 10 after the initial hemorrhage, according to local guidelines. In case of the occurrence of a DND when vasospasm is assumed to be the cause, angiography may be performed at any time. If it is performed earlier than day 7 to 10 and the patient shows no clinical deterioration thereafter, the angiography on day 7 to 10 is omitted. Treatment of radiographically confirmed vasospasm is according to local guidelines and not specified in the Earlydrain study protocol. It may include augmentation of cerebral blood flow via hypertensive hypervolemia as well as endovascular balloon dilation or intraarterial infusion of vasodilators.

After cerebrovascular imaging on day 7 to 10 the lumbar drainage of CSF is stopped in the LD-group. If cerebrovascular imaging is carried out before day 7, lumbar drainage is stopped on day 8. It may be pursued on a clinical base, as required.

### Amount and duration of CSF drainage

Patients randomized to the lumbar drainage group shall receive a daily drainage of 120 ml CSF, or 5 ml per hour for seven days. If higher amounts of CSF need to be drained on clinical grounds as in patients with hydrocephalus, this is preferably performed via an external ventricular drain.

The drain is planned to remain in place until the control angiography on day 7 to 10 after the initial hemorrhage. The local investigator may decide to remove the drain earlier in patients fully mobilized without clinical necessity of CSF drainage. However, consecutive drainage should not be less than four days to achieve a valid study result. Lumbar CSF drainage may be prolonged beyond the control angiography on clinical requirement. The amount of CSF drainage may then be adjusted to clinical requirements and bears no further restriction.

Patients randomized to the control group should not receive a lumbar drain before the planned control angiography to be performed on day 7 to 10 after SAH. If the patient develops hydrocephalus, and no EVD was placed initially for CSF drainage, a lumbar drain may be installed at the discretion of the local investigator. These patients are analyzed in the intention-to-treat analysis, but are not suitable for the per-protocol analysis.

### Consent to study participation

Consent to study inclusion is sought after explanation and agreement to a specific aneurysm treatment. Thus, patients capable of consenting to the aneurysm treatment will be informed about the study details themselves and may or may not agree to participate. If a patient is incapable of consenting to the proposed treatment, the legal representative should be informed on the conditions of treatment choices and afterwards, on the details of the EARLYDRAIN study. A patient may be randomized if the legal representative gives informed consent to the study, based on the presumed will of the patient. If neither the patient is capable of giving informed consent nor a legal representative is available in due time, an independent physician not involved in the patient's treatment nor in the trial may be asked for study approval. The latter option reflects a distinct characteristic of German law and the local ethic committee may or may not permit this.

This option was introduced into the consent procedure because the aforementioned retrospective data on lumbar drainage for treatment of aneurysmal SAH suggests a potentially beneficial effect of the measure for the patient. Therefore it shall not be categorically withheld from patients who are not capable of deciding whether to participate in the study or not and who do not have a legal representative.

However, in these cases of deferred consent, a legal representative needs to be established as soon as possible, according to German law. From our experience this legal procedure requires a time period from proposal to establishment of a legal representative of up to 72 hours, thus requiring the consent of an independent physician upfront for study inclusion. As soon as a legal representative is available and/or the patient is capable again to consent to the study, he or she must be asked to give informed consent. If the patient or his/her legal representative refuses consent after inclusion by advice of an independent physician, the patient's further study participation is no longer possible. In this case, however, the patient or his/her legal representative is asked to give consent for evaluation of already acquired data.

The detailed explanation of the study to the patient, legal representative or independent physician has to be carried out using appropriate explanations and words depending on the previous medical knowledge of the respective person and her/his level of education. During the explanations the respective person will be asked on a regular basis if she/he understands the conveyed information and if any questions have arisen. In addition to these verbal explanations the patient/legal representative/independent physician will be given a leaflet containing the study details. After reading the leaflet the respective person will be given as much time as she/he demands for the decision on study participation.

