### Outcome assessment

The primary endpoint is disability after 6 months, assessed by the modified Rankin Scale [18] dichotomized at a score of 0 to 2 versus 3 to 6 (6 = death). Assessment is performed by a blinded investigator of the local study center by personal visit. Alternatively, a telephone questionnaire is suitable for outcome assessment using the modified Rankin Scale [19]. Outcome assessment is planned to be done on the whole dataset as well as in preplanned stratified subsets (i.e. for example clinical SAH grade according to the Hunt&Hess scale 1-2 vs. 3-5 [20], CT grading according to Fisher I-III vs. IV [21]).

Secondary outcome criteria are:

• Mortality after 6 months

• mRS score after 6 months as continuous variable

• Angiographic vasospasm on day 7 to 10, as defined by a caliber reduction by 33% or more compared to the initial digital subtraction angiography

• Endovascular rescue therapy performed due to proven vasospasm, using balloon dilation of spastic vessels and/or arterial infusion of vasodilators

• Infarction (due to vasospasm) in the last CT scan before discharge

• Expression of clinical delayed neurological deficit after the aneurysmal SAH until discharge from acute care.

• Daily course of TCD mean flow velocity in both MCA at a depth of 50-60 mm

• Rate of death during the initial hospital treatment after the aneurysmal SAH.

• Rate of CSF shunt insertion during the first six months

• Presence of CSF infection during the first 14 days, as defined by modified CDC criteria for device-associated meningitis (treatment required on either positive culture, or elevated cell count, red cell/white cell ratio, increased lactate and/or decreased glucose) [22].

The following parameters will be recorded and used in predictor-/association models concerning primary and/or secondary outcome parameters:

• Gender

• Age

• Hunt&Hess grade on admission

• Time from symptom onset to admission

• Location of aneurysm

• Time from symptom onset to aneurysm treatment

• Treatment of aneurysm by clipping or coiling or both

• Time from symptom onset to randomization

• Time from symptom onset to treatment start (i.e. insertion of the lumbar drainage in the treatment arm)

• Time from admission to discharge

• Insertion of EVD (yes/no)

• Duration of EVD being in place

• Duration of lumbar drainage

• Amount of CSF drained by EVD [ml]

• Amount of CSF drained by lumbar drain [ml]

• Use of nimodipine (yes/no)

• Use of statins (yes/no)

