### Statistical Analysis

All data are described according to their mean, median or frequency, as applicable. The dichotomized modified Rankin score as primary outcome variable is investigated in using univariate analysis. Multivariate logistic regression modeling is performed accordingly, adjusted for clinical grade, fisher grade, ventricular hemorrhage, parenchymal hemorrhage, gender, nimodipine or other concomitant medical treatment. Analysis is planned as intention-to-treat as well as per protocol, excluding the patients who were treated with amounts of CSF drainage via lumbar drain deviating from the specified 5 ml/h or which needed a lumbar drain when randomized to the No-LD group.

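### After refused deferred consent the protocol asks only for data already acquired, so the 6-month mRS of surviving refusers is usually lost, possibly unequally by arm

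*Protocol article*

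**What the plan says.** The protocol article, Consent to study participation, lets an independent physician approve inclusion when the patient cannot consent and no legal representative is available in time. The route is meant for "patients who are not capable of deciding whether to participate in the study or not and who do not have a legal representative". It depends on the site, since "the local ethic committee may or may not permit this". On timing, the authors report that "this legal procedure requires a time period from proposal to establishment of a legal representative of up to 72 hours". Consent must then be sought: "As soon as a legal representative is available and/or the patient is capable again to consent to the study". No latest date is set.

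If consent is refused at that point, "the patient's further study participation is no longer possible". The patient or representative then "is asked to give consent for evaluation of already acquired data". No other permission is mentioned.

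Three other sections bear on this:
- **Outcome assessment:** the primary endpoint is the mRS at 6 months, 0 to 2 versus 3 to 6, with death scored 6. A visit is not essential: "Alternatively, a telephone questionnaire is suitable for outcome assessment using the modified Rankin Scale".
- **Interventions; Amount and duration of CSF drainage:** the drain is inserted during the anesthesia for aneurysm treatment and is planned to stay until the control angiography on day 7 to 10. Controls should have none before then.
- **Statistical Analysis:** "Analysis is planned as intention-to-treat as well as per protocol".

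**The concern.** Refusing the study treatment and refusing one later outcome contact are different decisions, but the rule treats them as one. It asks for what already exists and does not ask for the one item that the primary analysis needs. These patients have been randomised and belong in the intention-to-treat population.

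The refusal also comes after allocation, when the drain is normally either in place or absent at the bedside. A representative in one arm is asked to accept an invasive device. A representative in the other is asked to accept its absence, in a study whose stated rationale is possible benefit. Refusal rates could therefore differ by arm. If those lost also have a worse prognosis than the rest, the remaining comparison is distorted. An analysis plan can choose how to handle a missing mRS, but it cannot recover one that nobody was asked to allow.

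**Working it through.** **1. Which refusers lose the endpoint**

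- *Representative refuses after about 72 hours, patient alive:* the data acquired are days old, so the 6-month mRS does not exist and will not be collected.
- *Patient died before the refusal:* mRS 6 is already fixed and can be used if evaluation is permitted.
- *Patient regains capacity late and refuses after the 6-month assessment:* the mRS already exists and can be used if evaluation is permitted.
- *Evaluation of acquired data is also refused:* nothing can be used.

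The endpoint is therefore usually lost for surviving refusers, but not always.

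**2. The plan's own power figure** (Sample size calculation)

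Inputs: 300 patients, 50% versus 33% severe disability, alpha 5%. I take 150 per arm and a two-sided test; neither is stated. The formula for two proportions with pooled variance under the null, p̄ = 0.415, gives:

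z = [0.17 − 1.96 × √(2 × 0.415 × 0.585 / 150)] / √[(0.50 × 0.50 + 0.33 × 0.67) / 150] = (0.17 − 1.96 × 0.0569) / 0.0560 = 1.04

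Power = 85.2%, as stated. The calculation uses all 300 patients.

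**3. Number lost**

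The documents give neither the share entering by the deferred route nor the refusal rate. I assume 20–40% deferred and 5–15% of those refusing:

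- low: 300 × 0.20 × 0.05 = 3
- middle: 300 × 0.30 × 0.10 = 9
- high: 300 × 0.40 × 0.15 = 18

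**4. Power**

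With equal loss in both arms, the same formula gives 84.8% for 3 lost (148.5 per arm), 84.1% for 9 (145.5 per arm) and 82.9% for 18 (141 per arm).

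**5. Bias**

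Assume no true effect, 50% poor outcome in both arms (75 of 150), and 85% poor outcome among those lost. With k lost from an arm, its observed poor-outcome rate is (75 − 0.85k) / (150 − k):

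| k | Observed rate |
|---|---|
| 0 | 50.0% |
| 3 | 72.45 / 147 = 49.3% |
| 6 | 69.90 / 144 = 48.5% |
| 9 | 67.35 / 141 = 47.8% |
| 12 | 64.80 / 138 = 47.0% |
| 18 | 59.70 / 132 = 45.2% |

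Differences between arms, from unrounded rates, with the resulting two-sided type I error (normal approximation, unpooled variance):

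| Refusals | Split by arm | Spurious difference | Type I error |
|---|---|---|---|
| 3 | 3 : 0 | 0.7 points | 5.2% |
| 9 | 6 : 3 | 0.7 points | 5.2% |
| 18 | 12 : 6 | 1.6 points | 5.8% |
| 9 | 9 : 0 | 2.2 points | 6.7% |
| 18 | 18 : 0 | 4.8 points | 12.6% |

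With equal numbers lost per arm the spurious difference is zero under these assumptions. The last row is extreme: 18 refusals among 120 deferred patients, about 60 per arm, all in one arm, means 30% refusal there and none in the other, twice the assumed maximum of 15%. The planned effect is 17 points.

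**The case against.** Ending participation for someone who never gave valid consent is a legitimate rule, and the protocol does try to keep the data it has. An intention-to-treat plan does not oblige anyone to follow people who refuse. Missing-outcome handling belongs in an analysis plan that is not shown, and the consent form, where tiered options would normally sit, is not shown either. All of that is fair. Neither the respect for refusal nor the unseen missing-data method is criticised here. What stands is that the article states its rule expressly, names the permission to be sought, and that permission does not reach the endpoint.

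A reader might infer more than the text supports:

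- **That the endpoint is always lost.** Deaths before refusal and late refusals by recovered patients are exceptions.
- **That these are mostly severe patients.** Incapacity makes that plausible, but the criterion is incapacity together with no available representative. No grade or count is given, so the 85% figure is an assumption.
- **That the person deciding is told the allocation.** The text does not say so. It supports only that the drain's presence or absence is visible.
- **That the comparison is biased by 2 to 5 points.** That is the worst case, with every refusal in one arm.

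Whether German law and each local committee would allow a follow-up request after refusal cannot be judged from the document. The fix is conditional for that reason.

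**Conclusion.** The point holds in limited form. As written, the rule usually forfeits the 6-month mRS of surviving patients whose deferred consent is refused. It does so when allocation is visible, so the loss could differ by arm and could bias the intention-to-treat comparison. The document does not show that it will.

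The size cannot be derived from the document. On the assumptions above, a marked 2:1 imbalance among 9 to 18 refusals produces about 0.7 to 1.6 points, modest beside the planned 17. With 3 refusals the shift is at most 0.7 points even if all are in one arm. Power is a minor matter. The reason to act is that the loss can be avoided cheaply and cannot be repaired at analysis.

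**What to change.** In the section on consent and in the consent form, where the law and the local ethics committee permit, put two separate questions to anyone who refuses after inclusion on an independent physician's approval:

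(a) May the data already acquired be used?

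(b) May the single blinded 6-month mRS contact be made, by telephone if preferred, and vital status be obtained, with no study procedure in between?

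Keep those who agree to (b) in the intention-to-treat analysis with their outcome. Those who decline (b) remain refused. Report the number of refusals by arm.

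The cost is an ethics amendment, a change to the consent form and a few extra calls. The telephone mRS is already an accepted method in the protocol.
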